**Figure 3 F3:**
[figure not shown]
An overview and exploded view of the Fu's subcutaneous needling.

### Discontinuing interventions

3.8

The trial will be ceased if one of the following conditions appeared: a serious poststroke complication arises, or recurrent stroke or any other severe condition occurs leaving the patient in a critical condition.

### Outcome measures

3.9

The primary efficacy endpoint will be NRS at baseline, after the 1st treatment, after the final treatment and 4 weeks after the final treatment. The NRS is a segmented numeric version of the visual analog scale (VAS) in which a respondent selects a whole number (0–10 integers) that best reflects the intensity of pain. Thus, we select NRS as the primary measurement to assess the improvement of pain.

Secondary measurements will be as follows:

Fugl–Meyer score: The FMA score consists of 17 items, ranging from 0 to 34, with lower scores demonstrating poorer movement function. In our trial, we just assessed the upper extremity Fugl–Meyer which includes 10 items and ranging from 0 to 20 at baseline, after the final treatment and 4 weeks after the final treatment.

Constant score: A supplementary assessment of function of the shoulder joint will be assessed by the constant score scale at baseline, after the final treatment and 4 weeks after the final treatment.

Short-form of McGill pain questionnaire (MPQ-SF) score: The MPQ-SF is a multidescriptive measure of pain that consists of 22 pain questions. It reveals the nature of shoulder pain. It will be evaluated at baseline, after the final treatment and 4 weeks after the final treatment.

Quality of life (QOL) score: QOL will be evaluated using the Chinese version of EQ-5D-5L^[25]^ at baseline, after the final treatment and 4 weeks after the final treatment.

ROM: Pain-free passive range of motion (PROM) of the shoulder was designated as the ROM attained in the most painful position and was measured using a digital goniometer in 6 directions: flexion, extension, abduction, adduction, external rotation, and internal rotation. Five directions of the shoulder joint were measured (flexion, abduction, adduction, internal rotation, and external rotation), while participants were lying in a supine position. In addition, shoulder extension was measured in the side-lying position. PROM was also evaluated at baseline, after the final treatment and 4 weeks after the final treatment.

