**Methods::**

Here, we conduct a study design and protocol of a randomized, blinded, controlled study to evaluate the efficacy and safety of FSN in patients with HSP. A total of 60 patients with numerical rating scale (NRS) score above 1 will be recruited in the trial and randomized into FSN group or usual care (UC) group. Patients in the FSN group will receive FSN treatment combined with UC treatment while patients in the UC group will receive UC treatment alone for 4 weeks. The primary outcomes are changes of NRS at baseline, after the 1st treatment, after the final treatment and 4 weeks after the final treatment. Secondary measurements will be changes of Fugl–Meyer score, constant score, MPQ-SF score, quality of life score, and range of motion at baseline, after the final treatment, and 4 weeks after the final treatment. The safety will also be assessed by monitoring the incidence of adverse events and changes in vital signs during the study.

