### Sample size calculation

3.12

The trial is designed to determine the role of FSN for treating HSP among stroke survivors. Therefore, NRS change will be used as an evaluation index. According to our previous pilot study, the change of NRS before and after treatment in the treatment group was shown to be 3.40 ± 0.48 (n = 10) and that in control group was 3.10 ± 0.23 (n = 10). Sample size was estimated using the following formula: 

where n represents the number of samples required, n = n_1_ + n_2_, *Q*_1_ = n_1_/n, *Q*_2_ = n_2_/n with a significance level (*α* = 0.05) of a 2-sided 2-sample *t* test and 80% power to detect a difference between the 2 groups. Thus, a total sample size of 60 patients will be recruited allowing for 10% of attrition, with 30 in each.

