### Statistical analysis

3.13

The SPSS 20.0 (IBM SPSS Statistics, IBM Corp, Somers, NY) will be used to analyze the data. Quantitative data will be presented as mean ± standard deviation. NRS, Fugl–Meyer, Constant, MPQ-SF, QOL, and ROM scores will be conducted between the 2 groups by a superiority independent sample *t* test with a 95% confidence interval. The incidence of complications and adverse events will be compared by Chi-squared test. Any missing data will be replaced by the last measured value. For all analyses, *P* values of <.05 will be considered statistically significant.

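### Three post-baseline NRS times are all primary, with no time named and no rule for combining them, while the sample size covers a single 5% test

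*Protocol article*

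**What the plan says.** Section 3.9 (Outcome measures) defines the primary endpoint as follows: "The primary efficacy endpoint will be NRS at baseline, after the 1st treatment, after the final treatment and 4 weeks after the final treatment". The Methods part of the abstract gives the same list in the plural: "The primary outcomes are changes of NRS at baseline, after the 1st treatment, after the final treatment and 4 weeks after the final treatment".

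Section 3.13 (Statistical analysis) says that NRS and the other scores "will be conducted between the 2 groups by a superiority independent sample *t* test with a 95% confidence interval". On the threshold it says: "For all analyses, *P* values of <.05 will be considered statistically significant". It describes no order of testing, adjustment, joint model over time, or requirement on how many of the times must be significant.

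Section 3.12 (Sample size calculation) works from one quantity: "Therefore, NRS change will be used as an evaluation index". It takes pilot values for the change over treatment of 3.40 (SD 0.48) with FSN and 3.10 (SD 0.23) in the control group, 10 patients each. It then sets a 5% level "of a 2-sided 2-sample *t* test and 80% power to detect a difference between the 2 groups", and arrives at 60 patients, 30 per arm, with 10% attrition allowed for.

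**The concern.** Baseline precedes treatment, so it gives no treatment comparison. The other three times are all primary, and they answer different questions: the response to one session, the effect of the 4-week course, and whether that effect lasts. Because the plan does not say which of these decides the trial, a difference seen only after the first session could be reported as a positive primary result even if the groups did not differ at the end of treatment or at follow-up.

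The 5% level and 80% power in section 3.12 belong to a single test. They do not describe an endpoint that can be met in any of three ways.

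**Working it through.** **Inputs.** From the article: three post-baseline NRS times (section 3.9 and abstract); P<.05 for all analyses (3.13); two-sided test, 80% power, difference 3.40 − 3.10 = 0.30, SDs 0.48 and 0.23, 10% attrition, 30 per arm (3.12). Not in the article, so assumed: success means significance at any one time; each time gets its own two-sided t test; the correlation between times lies between 0 and 0.9.

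**Step 1: the plan's own sample size.** Pooled SD = √((0.48² + 0.23²)/2) = √0.14165 = 0.376. For one two-sided 5% test with 80% power, the noncentral t distribution gives 26 per arm. Allowing for attrition, 26/0.90 = 28.9, so 29 per arm, or 58 in total. This is within two patients of the stated 60. The stated size thus fits one test at 0.05.

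**Step 2: error rate for three independent tests.** Either direction: 1 − (1 − 0.05)³ = 1 − 0.857 = 0.143. In favour of FSN only: 1 − (1 − 0.025)³ = 1 − 0.927 = 0.073.

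**Step 3: allowing for correlation.** The same patients are measured each time, so the three test statistics are correlated. P(at least one |Z| > 1.96) and P(at least one Z > 1.96) were simulated for three standard normals with a common correlation, 2,000,000 draws each.

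| Correlation | Any false positive (nominal 5%) | In favour of FSN (nominal 2.5%) |
|---|---|---|
| 0 | 14.3% | 7.3% |
| 0.3 | 13.6% | 6.8% |
| 0.5 | 12.5% | 6.3% |
| 0.7 | 11.0% | 5.5% |
| 0.8 | 9.9% | 4.9% |
| 0.9 | 8.4% | 4.2% |

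A correlation that fades with distance in time (first-order autoregressive) gives similar two-sided figures: 12.9% at 0.5 and 11.4% at 0.7. Simulated t tests with 30 per arm also agree: 14.5%, 12.7% and 10.8% at correlations 0, 0.5 and 0.7.

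**Step 4: other success rules.** If all three times had to be significant, the rate could not exceed 5%, because it cannot be larger than the rate of any one test. If one time is named in advance, the rate is 5% with no change in sample size.

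**Step 5: keeping all three as primary with a Bonferroni split.** At 0.05/3 per test, the normal approximation gives 33 per arm; 33/0.90 = 36.7, so 37 per arm and 74 in total. With the planned 30 × 0.90 = 27 evaluable per arm, power per test would be about 70%, against about 83% at 0.05 by the same approximation.

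**The case against.** The strongest reply is that section 3.12 already points to one quantity, the change over treatment, so the end of treatment may be the intended primary time. That is a fair reading of intent, and the fix relies on it. But section 3.12 never names that visit as primary, and the abstract and section 3.9 both list all the times.

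A second reply is that a separate analysis plan may settle this. Here, however, the protocol itself fixes several primary times and a threshold for all analyses. A later plan that picked one time would be changing that text, not filling a gap.

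A third reply is that section 3.13 does not say in so many words that each time has its own t test. That is correct. It is the natural reading of an independent-sample t test applied to a score measured repeatedly, but it remains an inference and is listed among the assumptions.

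Three stronger readings are tempting and do not stand:

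- A reader might infer that the error rate simply is above 10%. The article gives neither a success rule nor a correlation, so the figure is conditional, and at correlations of 0.8 to 0.9 it falls below 10%.
- A reader might infer that the first-session comparison is unfair because one arm has just been needled. Sections 2.1 and 3.5 set up FSN plus usual care against usual care alone, so that difference is the add-on contrast under study.
- A reader might add every secondary score and each direction of shoulder movement to the count. Those outcomes are labelled secondary, nothing lets one of them establish efficacy, and section 3.13 does not say that the six directions are tested separately.

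**Conclusion.** The point holds in conditional form. The article makes three NRS times primary without naming one or saying how they combine, and its sample size and alpha cover only one comparison. If any one significant time suffices, the chance of at least one false-positive primary test is about 8% to 14% for between-time correlations of 0.9 down to 0, instead of 5%. In favour of FSN alone it is about 4% to 7%, instead of 2.5%. The success rule, the separate test per time and the correlation range are assumptions. The missing choice of a primary time is not: it follows directly from the text. It should be settled before recruitment because it decides what counts as a positive trial.

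**What to change.** In section 3.9 and the abstract, name the change in NRS from baseline to after the final treatment as the sole primary endpoint, tested at two-sided 0.05. This is the quantity closest to the one sized in section 3.12. Test NRS at the 4-week follow-up only if that test is significant. Make NRS after the first treatment a secondary outcome. State the same order in section 3.13.

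The cost is an amendment to the protocol and the registration, with ethics committee approval as section 3.15 requires. Section 4.1 says recruitment has not begun, so this can be done before the first patient. No patients or visits are added, whereas a Bonferroni split over three times would need about 74 patients. What is given up is that an effect seen only after the first session, or only at follow-up, could no longer carry the primary claim.

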### Safety assessment

3.10

Any adverse events, including hematoma, infection, dizziness, and apostasies will be evaluated during the whole treatment by the researcher. If any severe adverse events occurring, FSN intervention will be ceased immediately and the principal investigator will be informed to take proper actions. One month will be followed up after the trial in case of subsequent adverse events.

### Data collection

3.11

All the study data will be recorded on the CRF and any corrections made to the CRF must be personally signed and dated by the person responsible. All data will then be entered into a predesigned, password-protected electronic data set by 2 independent investigators who are blinded to group allocation. Double checking of entered data will be performed by another researcher to ensure accuracy.

### Sample size calculation

3.12

The trial is designed to determine the role of FSN for treating HSP among stroke survivors. Therefore, NRS change will be used as an evaluation index. According to our previous pilot study, the change of NRS before and after treatment in the treatment group was shown to be 3.40 ± 0.48 (n = 10) and that in control group was 3.10 ± 0.23 (n = 10). Sample size was estimated using the following formula: 

where n represents the number of samples required, n = n_1_ + n_2_, *Q*_1_ = n_1_/n, *Q*_2_ = n_2_/n with a significance level (*α* = 0.05) of a 2-sided 2-sample *t* test and 80% power to detect a difference between the 2 groups. Thus, a total sample size of 60 patients will be recruited allowing for 10% of attrition, with 30 in each.

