### Eligibility criteria

3.2

The inclusion criteria will be as follows: HPS induced by stroke; Duration ranges from 2 weeks to 6 months at time of recruitment; age ranges from 20 to 80; intensity of HSP evaluated by numerical rating scale (NRS) was above 1; adequate communication ability and intact cognitive function (Mini-Mental Status Examination scores ≥24 points); and signed informed consent.

The exclusion criteria will be as follows: HPS not induced by stroke; combination of heart, liver, or kidney failure endanger the safety of life at any time; younger than 20 years or older than 80 years; those who do not receive acupuncture therapy; women with pregnancy and lactation; participate in other studies; aphasia, and severe cognitive deficits.

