In our trial, strict quality control procedures have been applied to avoid bias, such as randomization and allocation concealment, assessor blinding and adequate sample size. However, methodologic limitations still exist. First, the trial is conducted in a single center. Thus, regional differences cannot be distinguished. Second, all the participants may have a higher expectation of acupuncture therapy because the trial was carried out in hospital of traditional Chinese medicine. Third, the therapists and the participants cannot be blinded in this study due to wide differences between FSN and UC treatment.

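### The pilot figures behind the sample size cannot be standard deviations of whole-number NRS changes, so the stated 80% power rests on invalid inputs

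*Protocol article*

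**What the plan says.** Section 3.12 (Sample size calculation) takes the NRS change before and after treatment from a pilot study: "treatment group was shown to be 3.40 ± 0.48 (n = 10) and that in control group was 3.10 ± 0.23", with 10 patients in each group. With a two-sided two-sample t test, alpha 0.05 and 80% power, it concludes that "a total sample size of 60 patients will be recruited allowing for 10% of attrition, with 30 in each".

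That section does not label the ± figures. Section 3.13 (Statistical analysis) uses the sign for the SD: "Quantitative data will be presented as mean ± standard deviation". Section 3.9 (Outcome measures) describes the NRS as a 0–10 scale on which "a respondent selects a whole number". Among the safeguards against bias, the Discussion lists "assessor blinding and adequate sample size".

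**The concern.** The difference between two whole-number ratings is a whole number. A mean of 3.40 or 3.10 over ten patients therefore forces some spread, because the patients cannot all sit at the mean. The printed ± figures look smaller than that unavoidable spread.

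The two figures are the only variability inputs to the sample size. If they are too small, the trial has less power than stated for the 0.30-point difference it was sized on. A non-significant result could then be taken as evidence against FSN when the trial was unlikely to detect that difference.

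**Working it through.** **Inputs.** Section 3.12: means 3.40 and 3.10 (difference 0.30), ± 0.48 and ± 0.23, n = 10 per group, two-sided alpha 0.05, 80% power, 10% attrition, 30 per arm (27 evaluable). Section 3.13: missing values are replaced by the last measured value, so up to 30 per arm could be analysed. The article's formula is missing from the text I had, so I used the standard two-sample calculation.

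**1. Reproducing the 60.** Pooled SD = √((0.48² + 0.23²)/2) = √0.14165 = 0.376. By the normal approximation, n per arm = 2 × (1.960 + 0.842)² × 0.14165/0.30² = 24.7, so 25. The t-based calculation gives 26. Allowing for attrition, 2 × 26/0.90 = 57.8, so 58, against 60 stated. Power at 27 per arm is 82%. The arithmetic from the printed inputs holds.

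**2. Smallest attainable SDs.** The tightest set of whole numbers uses only the two integers on either side of the mean.
- Mean 3.40 (sum 34): six 3s and four 4s. Sum of squares about the mean = 6 × 0.16 + 4 × 0.36 = 2.40. SD = √(2.40/9) = 0.516, or √(2.40/10) = 0.490 with divisor n. Printed: 0.48.
- Mean 3.10 (sum 31): nine 3s and one 4. Sum of squares = 9 × 0.01 + 0.81 = 0.90. SD = √(0.90/9) = 0.316, or √(0.90/10) = 0.300. Printed: 0.23.

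Both printed figures lie below the minimum with either divisor, and rounding does not close the gap.

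**3. Could they be standard errors?** Numerically, yes. The changes 1, 2, 2, 3, 3, 4, 4, 4, 5, 6 sum to 34 with sum of squares 136, so SD = √((136 − 115.6)/9) = 1.506 and SE = 1.506/√10 = 0.48. The changes 2, 2, 3, 3, 3, 3, 3, 4, 4, 4 sum to 31 with sum of squares 101, so SD = √((101 − 96.1)/9) = 0.738 and SE = 0.23. Working from the printed figures, the implied SDs are 0.48 × √10 = 1.52 and 0.23 × √10 = 0.73.

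**4. Power for 0.30 points.** Two-sided t test with noncentrality 0.30/(SD × √(2/n)) and 2n − 2 degrees of freedom:

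| SDs used | Pooled SD | Power, 27 per arm | Power, 30 per arm | Evaluable per arm for 80% |
|---|---|---|---|---|
| As printed, 0.48 / 0.23 | 0.376 | 82% | 86% | 26 |
| Smallest, divisor n − 1, 0.516 / 0.316 | 0.428 | 71% | 76% | 33 |
| Smallest, divisor n, 0.490 / 0.300 | 0.406 | 76% | 80% | 30 |
| If printed figures are SEs, 1.52 / 0.73 | 1.19 | 15% | 16% | 249 |
| Assumed SD 1.0 | 1.0 | 19% | – | – |
| Assumed SD 2.0 | 2.0 | 8% | – | – |

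The SDs of 1.0 and 2.0 are my assumptions, included to show a range.

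**5. Difference detectable with 80% power at 27 per arm.** About 0.78 points at SD 1.0, 0.92 at SD 1.19 and 1.55 at SD 2.0.

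**The case against.** The strongest objection is that section 3.9 defines the NRS for this trial, while section 3.12 says nothing of how the pilot recorded it. Averaged ratings or a continuous scale would permit the printed SDs. This stands as a stated assumption. Half-point scoring alone does not rescue the figures. In half-point units the mean 3.40 gives a sum of 68, and the sum of squares must be even; 470 gives SD 0.5 × √(7.6/9) = 0.46 and 472 gives 0.5 × √(9.6/9) = 0.52, so 0.48 is skipped.

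A reader might infer that 71% is the most power the trial can have. It is not. That value uses the n − 1 sample minimum at 27 per arm. Carrying the last value forward could keep 30 per arm (76%). The minimum for a population SD is the divisor-n value, which gives 76% at 27 and 80% at 30, so the extreme best case reaches the stated power.

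A reader might also take 15% as the trial's true power. The standard-error reading fits the numbers but is undocumented, and section 3.13 points to SD. A typing error or another scoring method would imply different values.

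Two further arguments do not show an error. A difference in group means may properly be smaller than one scale step. The entry rule ("intensity of HSP evaluated by numerical rating scale (NRS) was above 1") does not contradict the pilot figures, because the pilot's entry criteria and baseline scores are not given.

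**Conclusion.** The concern holds in a limited form. As SDs of single whole-number NRS changes in ten patients per group, 0.48 and 0.23 are impossible, so the 80% power has no valid basis as written. The fault lies in the inputs and not in the calculation made from them.

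The size of the shortfall is not known. With the smallest attainable SDs, power for 0.30 points is about 71–76% at 27 per arm and 76–80% at 30. Those cases need every patient to change by exactly 3 or 4 points, so real power is very likely lower. It would be about 15–16% on the standard-error reading, and about 19% to 8% at 27 per arm for an assumed SD of 1.0 to 2.0. The documents do not settle which of these applies. The impossibility itself rests on three assumptions: the same scale in the pilot, one rating per visit, and all ten patients per group contributing.

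**What to change.** Go back to the 20 pilot records and establish what 0.48 and 0.23 are: SDs, standard errors, a typing error, or figures from another way of scoring. Correct section 3.12, label the measure of spread, and state how the pilot NRS was recorded.

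Then recalculate, and state the power or the detectable difference that 60 patients deliver. If the pooled SD proves to be 1.19, for example, the text would say that 27 evaluable per arm give 80% power for about 0.92 points and about 15% for 0.30. In the Discussion, remove or qualify the claim of an adequate sample size unless the corrected figures support it.

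The cost is a check of the pilot records and revised wording. The downside is that the stated power will look less favourable. Restating what 60 patients deliver does not in itself require more patients.

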### Statistical analysis

3.13

The SPSS 20.0 (IBM SPSS Statistics, IBM Corp, Somers, NY) will be used to analyze the data. Quantitative data will be presented as mean ± standard deviation. NRS, Fugl–Meyer, Constant, MPQ-SF, QOL, and ROM scores will be conducted between the 2 groups by a superiority independent sample *t* test with a 95% confidence interval. The incidence of complications and adverse events will be compared by Chi-squared test. Any missing data will be replaced by the last measured value. For all analyses, *P* values of <.05 will be considered statistically significant.

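### The trial is sized on NRS change, but the endpoint and analysis sections name NRS scores, and no baseline adjustment is planned

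*Protocol article*

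**What the plan says.** Four places in the protocol article bear on what is compared between the groups.

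- **Abstract, Methods:** "The primary outcomes are changes of NRS at baseline, after the 1st treatment" and at two later times. The secondary measurements are also worded as changes.
- **Section 3.9 (Outcome measures):** the primary efficacy endpoint is the NRS itself at four times, one of which is baseline. Change is not mentioned.
- **Section 3.12 (Sample size calculation):** "Therefore, NRS change will be used as an evaluation index". The inputs are pilot changes: "in the treatment group was shown to be 3.40 ± 0.48 (n = 10") against 3.10 ± 0.23 (n = 10) in the control group, "with a significance level (*α* = 0.05) of a 2-sided 2-sample *t* test" and "80% power to detect a difference between the 2 groups".
- **Section 3.13 (Statistical analysis):** after listing NRS and the other scales, it says "ROM scores will be conducted between the 2 groups by a superiority independent sample" t test with a 95% confidence interval. It names no change score and no covariate.

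Section 3.9 has every efficacy outcome measured at baseline. Section 3.2 admits patients whose "intensity of HSP evaluated by numerical rating scale (NRS) was above 1". Section 3.3 describes no stratification by baseline pain.

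**The concern.** The sections that define the endpoint and the test point to scores. The abstract and the sample size point to change. These are different analyses with different standard deviations, and they can give different answers in the same data. While both remain open, the choice could be made after the results are seen.

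The power statement is tied to one of them. The SD of change leaves out the stable differences between patients in how much pain they start with; a follow-up score carries them in proportion to its correlation with baseline. A sample size built on the first need not serve the second. Under either reading, no analysis adjusted for baseline is planned, although the data for it will be in hand for every patient.

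**Working it through.** **Inputs from section 3.12.** Difference 3.40 − 3.10 = 0.30; change SDs 0.48 and 0.23; two-sided α 0.05; power 80%; 60 patients, 30 per arm, 10% attrition. Evaluable patients: 30 × 0.90 = 27 per arm.

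**Step 1: reproduce the plan's figure, on change.**
- Pooled change SD = √[(0.48² + 0.23²)/2] = √0.14165 = 0.376.
- Two-sample t test, 80% power (noncentral t): 26 per arm, 52 in total, and 52/0.90 = 57.8, so 58. The normal approximation gives 25 per arm, 50 in total and 56 after attrition.
- The stated 60 agrees to within 2 patients of the t-based figure.
- At 27 per arm the noncentrality is 0.30/(0.376 × √(2/27)) = 2.93, and power is 82%.

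The stated power therefore holds if change is tested.

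**Step 2: the same test on raw follow-up scores.** The noncentrality becomes 0.30/(S × √(2/27)), where S is the SD of the follow-up score. The document does not give S, so a range is assumed.

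| Follow-up SD (assumed) | Power at 27 per arm | Per arm for 80% (normal approximation) |
|---|---|---|
| 0.386 | 80% | – |
| 0.5 | 58% | 44 |
| 1.0 | 19% | 175 |
| 1.5 | 11% | 393 |
| 2.0 | 8% | 698 |

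The break-even SD is about 0.386. On a whole-number scale, an SD near that arises when about 82% of patients give one value and 18% the adjacent one: √(0.82 × 0.18) = 0.384. With entry open to any NRS above 1 on a 0–10 scale, so narrow a spread is hard to expect.

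**Step 3: ANCOVA with baseline NRS as covariate.** Assume equal SDs S at baseline and follow-up, with correlation ρ; the document gives neither. Fixing the change SD at 0.376 gives S = 0.376/√[2(1 − ρ)]. The ANCOVA residual SD is S√(1 − ρ²) = 0.376 × √[(1 + ρ)/2], which never exceeds the change SD. The one degree of freedom spent on the covariate is ignored.

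| ρ (assumed) | S | Raw score | Change | ANCOVA |
|---|---|---|---|---|
| 0.3 | 0.318 | 92% | 82% | 95% |
| 0.5 | 0.376 | 82% | 82% | 91% |
| 0.7 | 0.486 | 60% | 82% | 88% |
| 0.9 | 0.842 | 25% | 82% | 84% |

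All four rows share one model, so the columns can be compared. Where raw scores lose most (high ρ), ANCOVA gains much over raw scores but little over change. Where it gains most over change (low ρ), raw scores do not fall short.

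**Step 4: score or change as the ANCOVA outcome.** If Y is follow-up and B is baseline, regressing Y − B on treatment and B gives the same treatment coefficient and standard error as regressing Y on treatment and B. Only the coefficient of B shifts, by 1.

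**The case against.** The best defence is that section 3.13 lists instruments and does not say follow-up scores. The abstract and section 3.12 both name change, and 3.12 uses the same family of test as 3.13. Read together, they could supply the variable: the test is on change, baseline is used, and power is 82%. That reading is available. A reader might infer from 3.13 that the trial ignores baseline and misses its stated power. The document does not support that as a flat statement, because it holds only if raw scores are tested and only if their SD exceeds about 0.386.

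It is also fair that the document gives no baseline SD, follow-up SD or correlation, so the size of any loss is assumed. At correlations up to about 0.5 (equal SDs) raw scores keep 80%; those cases, however, imply a follow-up SD of 0.376 or less.

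A reader might further infer that chance imbalance in starting pain would bias an unadjusted comparison. It would not. Under randomisation the t test remains valid; imbalance costs precision, and it carries into follow-up scores only in proportion to their correlation with baseline.

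Finally, covariates are often left to an analysis plan, which is not shown here. That answers a complaint about missing detail. It does not answer the conflict, because this article states both an endpoint and a test and they do not match the quantity used for sizing.

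**Conclusion.** The point stands as an inconsistency in the primary analysis variable, together with a missed and inexpensive gain from baseline adjustment. Sections 3.9 and 3.13 name scores; the abstract and 3.12 name change.

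The stated 80% power is sound for a t test on change, given the pilot inputs. On the literal reading of 3.13 as raw follow-up scores it does not carry over, and the loss would probably be large: to 58% at an SD of 0.5 and 19% at 1.0. Those figures rest on assumed SDs and on that reading.

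ANCOVA has at least the power of the change test under equal SDs, from about 95% at a correlation of 0.3 to 84% at 0.9. The change should be made before the analysis is fixed. It is not a finding that the design is underpowered.

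**What to change.** In section 3.13, replace the unadjusted t test for the primary outcome with ANCOVA of post-treatment NRS on treatment group, with baseline NRS as covariate, and report the adjusted difference with its 95% confidence interval. Use the same form for each secondary score with its own baseline value.

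Align the wording of section 3.9, section 3.12 and the abstract with this analysis, so that all four places name one primary quantity. The sample size of 60 can stay: on its own inputs it supports a t test on change, and under equal SDs ANCOVA does at least as well.

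The cost is wording only. Baseline is already scheduled for every efficacy outcome, and no extra patients, visits or measurements are needed.

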**Discussion::**

Results from this trial will significantly support the application of FSN in the recovery of patients with HSP. If found to be effective and safe, FSN will be a valuable complementary option for patients with HSP.

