**Figure 1 F1:**
[figure not shown]
Schedule of enrollment, interventions, and assessments.

The study will commence on June 1, 2019, and will be completed by December 31, 2020, at GuangDong Second Hospital of Traditional Chinese Medicine. Sixty patients who meet the eligibility criteria and sign an informed consent form will be randomly divided into 2 groups to receive either FSN combined with UC or UC treatment alone in a 1:1 ratio. The flowchart of the trial is shown in Figure 2.

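### Adverse events are to be compared by a chi-squared P value alone, which at 30 per arm cannot support a conclusion about safety; interval estimates should carry that conclusion

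*Protocol article*

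**What the plan says.** Section 3.13 of the protocol article (Statistical analysis) fixes the comparison: "The incidence of complications and adverse events will be compared by Chi-squared test". It closes with a rule for every analysis, that P "values of <.05 will be considered statistically significant". The 95% confidence interval in the same section is attached to the independent-sample t tests of NRS, Fugl–Meyer, Constant, MPQ-SF, quality of life and range of motion. None is attached to event incidence.

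Section 2.1 names efficacy and safety together as what the trial evaluates. The Discussion paragraph of the abstract says: "If found to be effective and safe, FSN will be a valuable complementary option for patients with HSP". Section 3.10 names the events of interest: "Any adverse events, including hematoma, infection, dizziness" and others, with a further month of follow-up. The abstract's Methods paragraph adds vital signs, for which no analysis is named.

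Section 3.12 sizes the trial on NRS change only: "a total sample size of 60 patients will be recruited allowing for 10% of attrition, with 30 in each". No adverse-event rate is given anywhere.

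**The concern.** Safety is half of the stated objective, but the only inferential result planned for it is a yes-or-no comparison with 0.05. In a trial sized for a pain score, such a comparison will usually be non-significant whether or not FSN adds harm. The P value does not show how large an excess the data leave open; an interval does.

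What is at stake is what the trial can conclude. If a result above .05 were the only safety evidence, a statement that FSN is safe would rest on the trial's small size and not on its data.

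**Working it through.** **Inputs from the document.** 60 patients, 1:1, so 30 per arm (sections 2.2 and 3.12); 10% attrition, so about 27 completers per arm (3.12); chi-squared test at P<.05 (3.13).

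**Assumed inputs.** All event rates, because the document gives none. A range is shown.

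**The plan's own figure.** There is no figure for safety. The 60 comes from NRS: difference 3.40 − 3.10 = 0.30, SDs 0.48 and 0.23, two-sided 0.05, 80% power. An unequal-variance t calculation gives 27 per arm, and 27 / 0.90 = 30 per arm, 60 in total. So 60 reproduces, but it says nothing about events.

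**Step 1: chance of detecting an excess.** For true rates p (FSN) and q (usual care), add Bin(a; 30, p) × Bin(b; 30, q) over all pairs (a, b) with P<.05. Chi-squared is taken without continuity correction, since 3.13 mentions none.

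| True rates, FSN v usual care | Chi-squared | Fisher |
|---|---|---|
| 10% v 2% | 21.8% | 4.3% |
| 15% v 5% | 26.4% | 9.3% |
| 20% v 5% | 45.3% | 24.1% |
| 30% v 10% | 50.0% | 37.2% |

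With 27 per arm, chi-squared falls to 17.9% for 10% v 2% and 23.5% for 15% v 5%.

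**Step 2: what a clean result leaves open.** With 0 events in n patients, the exact (Clopper–Pearson) two-sided 95% upper limit is 1 − 0.025^(1/n). For n = 30 this is 11.6%; for n = 27 it is 12.8%. With 1 event in 30 it is 17.2%.

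**Step 3: what an interval adds to a P value.** Take 3/30 v 0/30. Chi-squared gives P = 0.076, not significant. The Newcombe 95% interval for the risk difference is −3% to 26%. The P value alone hides that an excess of 26 percentage points is not excluded.

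**Step 4: is chi-squared itself at fault?** With equal rates in both arms, the Step 1 sum gives its actual false-positive rate at 30 per arm: 0.3% (rate 2%), 2.8% (5%), 5.4% (10%), 5.3% (15%), 4.9% (20%), 4.9% (30%). It is not materially inflated. Fisher's rate over the same range is 0.0% to 2.6%, well under the nominal 5%.

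**Step 5: sparse tables.** P values by test:

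| Events | Chi-squared | Fisher | Barnard (unconditional) |
|---|---|---|---|
| 4 v 0 | 0.038 | 0.112 | 0.046 |
| 5 v 0 | 0.020 | 0.052 | 0.022 |

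Barnard's exact test stays close to chi-squared; Fisher is the outlier. If usual care has no events, chi-squared needs at least 4 FSN cases. At a true FSN rate of 10% the chance is P(X ≥ 4) = 35% for X ~ Bin(30, 0.10). Fisher needs 6 cases, and the chance falls to 7%.

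**The case against.** **No rate is given, so few events is an assumption.** This stands. Section 3.6 allows traditional acupuncture in both arms, so needling events can occur under usual care too. FSN is given 20 times (5 a week for 4 weeks, section 3.7); at an assumed independent risk of 1% to 2% per session, 1 − 0.99^20 = 18% to 1 − 0.98^20 = 33% of FSN patients would have an event. The point does not need rare events: at 20% v 5% and 30% v 10%, chi-squared still misses about half of real excesses.

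**A reader might infer that P is unreliable because expected counts are small.** With 30 per arm, any event type with fewer than 10 cases in total has expected counts below 5. But Step 4 shows the false-positive rate holds, and Fisher's larger P values reflect its own conservatism.

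**A reader might infer that the plan will treat a non-significant test as proof of safety.** No section says so. The abstract's sentence is conditional and states no criterion.

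**Low power comes from the sample size, and no test choice cures it.** True, which is why the remedy is an interval and not another test.

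**Intervals and tables by event type may sit in an analysis plan not shown here.** They may. The article nevertheless names the safety test and its threshold and gives an interval to efficacy only; an analysis plan that followed it would carry the weakness forward. This argues for minor severity.

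**Conclusion.** The concern holds in a limited form. A chi-squared P value is the only analysis fixed for complications and adverse events, and at 30 per arm a non-significant result could not support a conclusion on the safety half of the objective. Its chance of detecting an excess is about 22% for 10% v 2% and 26% for 15% v 5%, and at most about 50% in the wider pairs tabulated. No events in 30 FSN patients leaves a rate up to 11.6% open.

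The power figures rest on assumed event rates and on chi-squared without correction; the 11.6% limit rests only on 30 patients observed. The test's error rate is sound. Severity is minor: nothing in the document is contradicted, but a better and nearly free analysis exists for a stated objective.

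**What to change.** In section 3.13, replace the sentence on adverse events with wording to this effect: for any event and for each event type, report the number of patients affected in each arm, an exact 95% confidence interval for the FSN-arm rate, and the risk difference with a score-based (Newcombe) 95% interval. State that the safety conclusion rests on the upper confidence limits and that P>.05 is not evidence of safety.

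Do not switch to Fisher's test; it would lower the chance of detecting harm further. If an exact P value is wanted for sparse tables, name one unconditional exact test in advance (Barnard or Boschloo). The choice matters near the threshold: for 4 v 0, Barnard gives 0.046 and Boschloo 0.070.

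**Cost.** A few lines of analysis, with no change to sample size or data collection. The safety claim becomes more modest. An interval and a P value can also disagree at the margin: for 4 v 0 the Newcombe interval is about −1% to 30% although chi-squared gives 0.038. This is a further reason to say beforehand that the interval governs.
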